## Abstract

The majority of mental illnesses begins in childhood, adolescence and young adulthood before the age of 25. The transition from adolescence to adulthood is a particularly vulnerable time for adolescents with mental illness, affecting psychosocial functioning and participation in work life. Therefore, they need—in contrast to classic standard vocational interventions—a long-term, holistic and individually oriented vocational rehabilitation program. With the innovative model project "Start in education and employment (StAB)”, adolescents and young adults with mental illnesses are to be supported with regard to their vocational perspectives and participation by a new type of individualized, holistic, long-term job coaching. It follows the Individual Placement and Support (IPS) concept, as a manualized form of the Supported Employment Approach and is based on the "first place–then train" principle. In order to evaluate the effectiveness and feasibility of the StAB program, a double-centre prospective single arm evaluation study in a mixed-methods design will be conducted. The focus is on quantitative research analysing pre-post-effects of the StAB intervention in a two-year observational study. Young people between 15 and 25 years with a psychiatric diagnosis who are currently in receipt of means-tested benefits or are entitled to them will be recruited. The study will take place in two major cities in the north-western part of Germany, Bielefeld and Dortmund. We expect to contribute to gain more empirical data about the implementation of Supported Employment and Education to severely mentally ill adolescents and young adults in German settings. Moreover, these results may also provide the scientific foundation for future measures focusing the improvement of vocational rehabilitation for young people with mental illness.

The study was registered in the German Clinical Trials Register (DRKS00027576) on March 10, 2022.

## Introduction

The majority of mental health illnesses have their roots early in life. In fact, it has been found that 75% of all psychiatric disorders begin before the age of 25 [1–3]. This period between the ages of 15 and 25 years is a sensitive phase in everyone’s life, in significant neurobiological, cognitive, social and legal changes are imminent and different developmental milestones need to be achieved [4]. However, for young people with mental illness, the transition from adolescence to adulthood is particularly challenging because of diminished social skills and coping strategies compared to their not affected (healthy) peers [5] and they have to face great difficulties in gaining access to mental health services [6]. Moreover, mental illnesses are often accompanied by serious impairments of psychosocial functioning, which in turn makes it difficult to participate in various areas of life. For example, mental health problems are often associated with negative effects on the educational and employment situation [7]. As a result, limited participation in working life is accompanied not only by economical losses, but also by the absence of psychosocial benefits, such as access to social networks or a sense of purpose and meaning. As Lloyd and Waghorn (2007) have pointed out, work has an important role in recovery and rehabilitation, because “*having a reason to get out of bed and something meaningful to do during the day is essential for the well-being of people with mental illness*” [8] (p. 127). However, adolescents with psychiatric disabilities often face significant barriers to employment, e.g. lack of work experience, transportation problems, lack of clear responsibility for promoting vocational development or psychiatric symptomatology not being well controlled [8, 9]. On the other hand, research has shown that access to employment support programs for young people with mental illness may be associated with higher vocational success rates and improved long-term employment outcomes [10].

Whereas traditional vocational rehabilitation programs train people in certain required skills before (re)placing them in jobs, the supported employment (SE) approach foregoes any extended preparation but concentrates on placing participants in the labour market as soon as possible [11]. Systematic reviews revealed that the Individual Placement and Support (IPS) program, as a manualized form of SE, is highly effective in comparison to other regular “first train–then place” rehabilitation programs [12, 13]. The central features of IPS are: eligibility based on client choice, focus on competitive employment, integration of mental health and employment services, attention to client preferences, work incentives planning, rapid job search, systematic job development, and individualized job supports [14]. Although IPS has become a well-established practice model and is widely applied to help adults with severe mental illnesses [15, 16], evidence on its effectiveness for adolescents and young people is still sparse [17–19] especially in Germany [20]. The German social and health care system, similarly to other European countries [21], is very fragmented and characterized by different intersections, leading to discontinuities and gaps in the psychosocial care of people with mental health difficulties [22]. Therefore, a long-term, coordinated, holistic and individualised support for education and employment is of high relevance during the vulnerable transition from adolescence to adulthood. With our study presented here, we want to contribute to the research and dissemination of an IPS oriented intervention for young people with mental health difficulties between the ages of 15 and 25. The study protocol for the evaluation of this innovative support program is described throughout the present paper. This study protocol is the first version (16.05.2022).

## Materials and methods

### Objectives

The main objective of this study is to evaluate the effectiveness and feasibility of the StAB project (German: Start in Ausbildung und Beruf, [= Start in education and employment]), a supported employment and education intervention for mentally burdened adolescents and young adults. Based on the IPS approach, StAB aims at facilitating entry or re-integration to the general labor market or regular vocational training.

We assume that the intervention will result in an increased psychosocial participation and functioning of the participants (primary outcomes). At the same time, barriers and inhibiting living conditions are expected to decrease, so that quality of life, self-efficacy and other dimensions of the participants will improve. In terms of occupational parameters, we expect at least 40% of the participants to have completed education or vocational training or a specific preparatory internship, or to have returned to work or are employed at the primary labour market within two years after program enrolment. In addition, the effects of the intervention will be analyzed regarding further outcome variables, e.g. self-esteem, psychopathological symptoms or need for inpatient treatment.

The StAB project also aims to structurally change the local health and social care system. For this purpose, the implementation of a cross-sector competence network with relevant stakeholders and key informants from the fields of pediatric and adolescent medicine, child and youth work, education, vocational rehabilitation, and psychosocial support is planned.

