### Sample size

With regard to the central outcome parameters, an improvement in the questionnaire results (e.g. psychosocial participation and functioning, quality of life, self-efficacy) between the initial and final assessment is expected over the two-year StAB intervention period. Thus, considering A) a paired t-test for dependent samples as the statistical analysis method, B) a small to medium effect size (d = 0.4), C) an α-(error) level of 0.05, and D) a β-level of 0.2 (or a power of 0.8), the a priori case number estimation using the programme G*Power 3.1 [23] resulted in a required sample size of n = 52 persons. Assuming a dropout rate of at least 30% during the 24 months period after recruitment, at least 75 people should be included into the study.

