**ASSESSMENTS**				
Psychosocial participation and functioning	IMET	✓		✓
	WHODAS 2.0	✓	✓	✓
Mental health status	PHQ-9	✓	✓	✓
	SCL-K-9	✓	✓	✓
	L-1	✓	✓	✓
	SCIP	✓		✓
	AMS-R	✓	✓	✓
Self-esteem and self-efficacy	G-SISE	✓	✓	✓
	ASKU	✓	✓	✓
Psychosocial resources	Social contacts (LK-18)	✓	✓	✓
	BRS	✓		✓
	HLS-EU-Q16-GER	✓		✓
Study-specific questionnaires	Demographics, Professional biography, Work ability, Satisfaction with medical care, Work and employment prospects under corona conditions	✓	(✓) partially	✓

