#### Measures

Table 1 shows the questionnaires as well as their measurement time point within the study.

*Psychosocial participation and functioning*. Developed by the WHO, the **WHODAS 2.0** (*World Health Organization Disability Assessment Schedule 2*.*0*) is an assessment instrument to measure health, functional impairment and disability across diseases, countries, and cultures in accordance with the International Classification of Functioning, Disability and Health (ICF) [28]. In our study we use the 12-item self-report version, that has been found to explain 81% of the variance of the most widespread 36-item version [28]. The 12-item WHODAS 2.0 presents high internal consistency (up to 0.96), reliability, sensivity to change as well as overall good correlations with other measures of disability [29].

The **IMET** (*Index zur Messung von Einschränkungen der Teilhabe*, German for: Index for the Assessment of Health Impairments [30]) was developed to assess participation and involvement for patients with different (chronic) diseases as described by the ICF. The extent of impairment in nine areas of everyday activities (e.g. family/household obligations, recreational and leisure activities) have to be indicated on an 11point scale from 0 = no impairment to 10 = no more activity possible. Cronbach’s alpha was .90 - .91. Convergent validity is supported by moderate to high correlations of the IMET total score with earning capacity and performance measures. Furthermore, normative data from a population-based survey allows classification of participation impairment [31].

*Mental health status*. For assessing the burden of psychopathology, the *9-item short version of the Symptom Checklist* (**SCL-K-9**) is used [32]. This short scale measures the subjectively perceived impairment by physical and psychological symptoms within a period of seven days. The SCL-K-9 exhibits satisfactory psychometric properties and its summed up total score is highly correlated with that of the original 90 items questionnaire (r = .93) [32], thus representing a Global Severity Index (GSI, [32]).

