#### Data analyses

Before data analysis, the data set will be inspected with regard to inconsistencies and missing values. Missing data will be addressed by applying linear mixed models, if appropriate. We will perform a dropout analysis to check for differences between program completers and non-completers with regard to main demographic, psychosocial, and work-related variables. Besides descriptive baseline data analysis, we will primarily analyse changes in the main outcome measures from baseline to final assessment (after up to a maximum of 2.5 years). Theses analyses on the study outcome measures will be performed as intention-to-treat, supplemented by a “per-protocol”-analysis including all individuals who have completed the StAB program without dropping out. Of course, a repeated-measures approach is used if indicated. Program effects on outcome measures will be explored by taking into account relevant covariates, like key baseline variables, changes in some measures within the first year (see above) or program specific variations, e.g. number and total duration of coaching sessions. Program feasibility and acceptance among the participating adolescents and young adults with mental health difficulties will be evaluated using process documentation data as well as subjective ratings in the final assessment.

The statistical analysis of the data will be done using the software package IBM SPSS Statistics Version 25 and the level of statistical significance will be set to p < .05.

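### The primary outcomes are plural with no single primary instrument named, while the sample size and the 5% level are set for one test, so the stated alpha and power hold per test and not for the primary claim

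*Protocol article*

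**What the plan says.** Four places in the protocol article bear on this.

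- **Objectives.** The assumption is that "the intervention will result in an increased psychosocial participation and functioning of the participants (primary outcomes". The tag is plural and attaches to a construct. Quality of life and self-efficacy follow in a separate sentence without the tag, and self-esteem, symptoms and inpatient need are called further outcomes.
- **Table 1 and Measures.** The row group "Psychosocial participation and functioning" contains IMET (T0 and T2) and WHODAS 2.0 (T0, T1 and T2). Measures describes both under the same heading: WHODAS 2.0 "is an assessment instrument to measure health, functional impairment and disability across diseases, countries, and cultures", and IMET "was developed to assess participation and involvement for patients with different (chronic) diseases". Neither is put first, and no composite is defined.
- **Sample size.** The opening refers to several outcomes: "With regard to the central outcome parameters, an improvement in the questionnaire results (e.g. psychosocial participation and functioning, quality of life, self-efficacy". One paired t-test at alpha 0.05 with power 0.8 and d = 0.4 then "resulted in a required sample size of n = 52 persons", raised to at least 75 for 30% dropout.
- **Data analyses.** The primary analysis is of change in the main outcome measures, again plural, from baseline to final assessment, and "the level of statistical significance will be set to p < .05". The article states no order of testing, no division of alpha, and no rule for when the primary hypothesis counts as supported.

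**The concern.** A sample size for one test fixes the error rate and power of one test. Here the primary construct has two candidate scales, and the text does not say whether improvement on one is enough or both must improve. The two rules have different consequences. If one scale is enough, the chance of a false positive on the primary hypothesis exceeds 5%. If both are needed, the chance of success is below the 80% on which 52 was based.

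The labels add to the ambiguity. The outcomes are primary in Objectives, central in Sample size and main in Data analyses, and the Sample size list is broader than the set tagged primary. With about a dozen questionnaires in Table 1 and no control group, fixing one primary scale in advance is one of the few protections against a headline chosen after the results are known.

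**Working it through.** **Inputs.** From Sample size: d = 0.4, alpha 0.05, power 0.8, n = 52, 30% dropout, 75 enrolled. From Table 1: two scales under the primary label. The correlation between the changes on the two scales is not given, so I assume r from 0 to 0.9.

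**1. The plan's own figure.** For a paired t-test, df = n − 1 and the noncentrality is d√n. At n = 52 this is 0.4 × √52 = 2.884, with two-sided 5% critical value t(51) = 2.008. Power is 0.808; at n = 51 it is 0.7999. So 52 is the smallest n that reaches 80%, and the test is two-sided (one-sided would need 41). Enrolment: 52 / 0.7 = 74.3, rounded up to 75. Both figures reproduce.

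**2. Either scale suffices, each at two-sided 0.05.**

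- Independent: 1 − 0.95² = 0.0975.
- Correlated (bivariate normal): 0.10 − P(both reject) = 9.1% at r = 0.5, 8.3% at r = 0.7, 7.0% at r = 0.9.
- Counting only false improvements, the direction of the hypothesis: 2 × 0.025 − P(both exceed the upper limit) = 4.9% at r = 0 and 3.5% at r = 0.9, against 2.5% for one test.
- True power under this rule rises. If d = 0.4 on both scales, the chance that at least one is significant is 96% at r = 0 and 86% at r = 0.9.

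**3. Both scales required, each at two-sided 0.05.**

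- At the planned 80% each: 0.8² = 64% at r = 0, 71% at r = 0.7, 75% at r = 0.9.
- At the actual 80.8% each: 0.808² = 65% at r = 0, 76% at r = 0.9.
- For 80% joint power with independent scales: 67 completers, 67 / 0.7 = 95.7, so 96 enrolled.

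**4. Alpha split equally (0.025 each).**

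- The critical value becomes t(51) = 2.310, and power per scale at n = 52 is 71.6%.
- For 80% per scale: 62 completers, 62 / 0.7 = 88.6, so 89 enrolled.

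**5. One named primary, the other tested only after it succeeds.**

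- Family-wise error stays at 5% or less, because the second test is reached only through the first.
- Power for the primary stays 80.8% at n = 52. The chance that both are significant is the joint power in step 3, 65% to 76%.

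**The case against.** The case on the other side has several good parts.

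- **The article does not call WHODAS 2.0 and IMET primary.** Correct. A reader might infer that both are designated primaries, but the article tags a construct, and the link to the scales runs through the shared label in Table 1. What stands is that no instrument is designated.
- **The wider list is not a set of co-primaries.** Also correct. A reader might count four central constructs and quote a family-wise error of 13% to 19%. The documents do not support that. The list is open, Table 1 treats participation and functioning as one domain, and Objectives does not tag quality of life or self-efficacy as primary. What remains is a mismatch between the two sections.
- **No stated operating characteristic is literally broken.** Each single test keeps 5% and 80.8%, and the article never claims family-wise control or joint power. Power falls only if both scales are required or alpha is split, and the article says neither.
- **The two-sided figures include false deteriorations.** For false improvement the range is 4.9% to 3.5%. That is still above the nominal 2.5%.
- **Multiplicity detail may be in an analysis plan that is not shown.** A missing adjustment alone would be no finding. But the plural primary, the one-test sizing and the differing outcome lists are stated here. An analysis plan that split alpha or required both scales would leave 52 too small for 80% power.
- **This is a single-arm pre-post evaluation that also examines feasibility.** The Discussion concedes that confounders cannot be controlled and that a randomised trial should follow. That lowers the severity. It does not remove the point, since Objectives makes effectiveness a main aim and Sample size makes a formal power claim.

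**Conclusion.** The point holds in limited form. The sample size arithmetic is correct for one two-sided paired t-test. The primary outcome is stated in the plural, two unranked scales sit under its label, and the outcome list in Sample size differs from Objectives. The 5% and 80% therefore apply to each test and not to the primary claim.

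For two scales and an assumed correlation of 0 to 0.9, family-wise two-sided error is about 9.8% to 7.0% if either suffices. If both must succeed at 80% power each, joint power is about 64% to 75%. An equal split of alpha gives 72% per scale at n = 52. These figures assume 52 completers, d = 0.4 on both scales for the power results, and that the two scales in Table 1 are the measures of the primary construct.

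This should be fixed. It is not a fatal defect, given the uncontrolled design.

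**What to change.** Before any outcome data are seen:

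1. Name one primary instrument, WHODAS 2.0 or IMET, as change from T0 to T2. Both are measured at those visits, so either can serve. The extra T1 measurement of WHODAS 2.0 is not a strong reason to prefer it, because the main contrast is baseline to final.
2. Test the other scale only if the first is significant, each at two-sided 0.05.
3. Label quality of life, self-efficacy and all other scales secondary or exploratory. They may still be tested and reported as such.
4. Make the outcome wording in Sample size and Data analyses match Objectives, with one term for the primary outcome throughout.

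The cost is wording in the protocol and the registry entry. The 52 completers and 75 enrolled stay, as do the stated alpha and power for the primary test. The downside is that the second scale loses equal standing. If the sponsor wants both scales on an equal footing, it should state the success rule and re-size: 62 completers (89 enrolled) for an equal alpha split, or up to 67 (96 enrolled) if both must succeed.

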### Study design and setting

The StAB supported employment and education program is realized by a mixed-methods design. Its main focus is a naturalistic, double-center prospective single arm evaluation study using a pre-post repeated measure design. Given the vulnerable target population of young people with different mental health problems, this study will also examine the feasibility of program implementation and does not include a control group. The establishment of a competence network will be supported by qualitative and quantitative surveys in order to identify the needs of stakeholders in the field of vocational integration and rehabilitation for young people with mental health problems. The study will take place in Dortmund and Bielefeld, two major cities in the north-western part of Germany. Recruitment is scheduled to begin during May 2022. The trial was registered at the German Clinical Trials Register on 10/03/2022 (DRKS00027576).

### Participants

To be eligible to the study, potential participants have to fulfil the following inclusion criteria: A) age 15–25 years, B) a psychiatric diagnosis (either currently or in the last 12 months) according to International Statistical Classification of Diseases and Related Health Problems (ICD-10) criteria, excluding acute intoxication and intellectual disabilities, C) receiving or currently applying for means-tested benefits (German: Arbeitslosengeld II), and D) sufficient written and spoken German language skills. All participants are required to read the study information and sign the consent form. For minors between 15 and 17 years of age, written informed parental consent is required.

### Sample size

With regard to the central outcome parameters, an improvement in the questionnaire results (e.g. psychosocial participation and functioning, quality of life, self-efficacy) between the initial and final assessment is expected over the two-year StAB intervention period. Thus, considering A) a paired t-test for dependent samples as the statistical analysis method, B) a small to medium effect size (d = 0.4), C) an α-(error) level of 0.05, and D) a β-level of 0.2 (or a power of 0.8), the a priori case number estimation using the programme G*Power 3.1 [23] resulted in a required sample size of n = 52 persons. Assuming a dropout rate of at least 30% during the 24 months period after recruitment, at least 75 people should be included into the study.

### Recruitment and study procedure

Participants will be recruited through local psychiatric clinics and the responsible job centers in both study sites. Involved staff members will be comprehensively informed about the project, e.g. during departmental or ward meetings, and receive written study information (project overview, inclusion criteria, access flow). When staff members have screened and identified patients matching the inclusion criteria, these potential participants will be provided with initial study information and then will get in contact with an IPS coach in order to receive more detailed oral and written information. Potential study participants will be given sufficient time to ask questions, and they also receive a detailed information sheet on the goals, nature, and implications of the study project as well as on data protection regulations. After the interested person has confirmed participation following an individual consideration and decision-making phase, and signed the informed consent, a study entry assessment appointment will be scheduled and the IPS coaching intervention (see next section) will start. As it is described in the study information, participants can leave the program at any time without any disadvantages arising for them. Recruitment is scheduled to begin in May 2022.

